### Subject withdrawal

The parents/guardians can withdraw the infant from the study at any time. Infants may be withdrawn from the study by the attending neonatologist or the PI for safety reasons, such as adverse events (AE) (clinical events or laboratory values), major protocol deviations, or significant deteriorations in the patient’s condition that warrant discontinuation of the intervention. The final examination/sampling at study termination must then be performed at the time of the study discontinuation. Infants who withdraw from the study will not be replaced.

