### Eligibility, randomization and blinding

Infants evaluated for eligibility for enrollment in the study will be identified at routine ROP screening by the local ophthalmologist. ROP evaluations will adhere to clinical screening practice according to national guidelines. RetCam will be used at the ROP screening to document the extent of ROP disease, and images will be saved in the clinical record file. When the ROP screening ophthalmologist evaluates eligibility, the PI and the steering group will be contacted. Images will be evaluated, and eligibility for inclusion must be confirmed by at least two of three ophthalmologists in the steering group.

Parents/guardians will be given oral and written information about the study via the HOPE Parent Application (Addi Medical) and asked to participate if the infant is eligible. The signed informed consent will be collected before any study-specific data is reported and the infant is randomized. Randomization will be performed stratified by centre by a study nurse using an electronic application (HOPE). After randomization, the study nurse will provide eye drops to the assigned neonatal nurse in the neonatal intensive care unit (NICU) for administration or to the parents or guardians if the infant is discharged from the hospital. In case of problems regarding the study eye drops, a randomization list is safely stored in a locker at the NICU and available 24 h/day in case of emergency and safety issues. All investigators, ophthalmologists, staff, and patients/guardians, except pharmacists, are blind to the participants’ eye drop assignments. The single-dose containers for dexamethasone and placebo are similar, and identification of drop content will not be visible to an untrained eye.

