### Safety outcomes in the intervention study

Clinically significant changes (abnormalities) from the physical examination of the infant or abnormal laboratory values will be recorded as an AE, starting from the time of randomization until the intervention phase termination visit. Ongoing AE at the intervention phase termination visit will be followed until the event is resolved or stable. Especially signs of increased ocular pressure (> 20 mmHg) or abnormal growth (> 1 standard deviation difference in weight, length and head circumference) after the start of intervention will be monitored as these are well-recognized side effects of high-dose steroid treatment, although this treatment is considered to be low dose. Other collected study-specific AEs will be pulmonary haemorrhage, pneumothorax, bronchopulmonary dysplasia (BPD), pulmonary hypertension, hypotension, circulatory instability, surgical patent ductus arteriosus (PDA), medical PDA, hypoglycemia, hyperglycemia, insulin treatment (glucose > 10 mmol/L at 2 independent time points), necrotising enterocolitis (NEC), perforated gut, ileus, enterostomy, sepsis, meningitis, intraventricular haemorrhage (IVH), and hydrocephalus. For each AE the following data will be recorded: AE diagnosis, AE start and end date, action taken regarding AE, AE outcome (resolved, ongoing, death, or lost to follow-up) and AE causality (not related, possibly related, related). Any severe AE (SAE), death or life-threatening event will be reported from the investigator at each site to the PI within 24 h of knowledge of the event. The local investigator and PI can stop the intervention temporarily or discontinue the infant from the study. If the infant is discontinued from the study, proper study termination procedures, including examinations and samplings, must be followed accordingly. The PI must report discontinuation due to an AE/SAE immediately to Thea Nordic.

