**Data collection and study procedures**									
Informed consent	X								
Eligibility	X								
Medical history/characteristics of infant/mother	X								
ROP evaluations	X		X	X	X				
RetCam photography	X		X	X	X				
Randomization		X							
Dexamethasone/placebo intervention dispense/return		X	X	X	X	X	X		
ROP treatment with laser and/or anti-VEGF			X^c^	X^c^	X^c^				
Intraocular pressure	X^d^		X^d^	X^d^			X^d^		
MRI^e^ + Peapod						X^e^			
Physical examination		X				X		X	X
Weight, length, head circumference		X	X	X	X	X		X	X
Vital signs: SpO2, heart rate, blood pressure		X					X		
Blood samples		X^f^	X^f^	X^f^	X^f^	X^f^	X^f^		
Saliva cortisol		X	X	X	X		X	X	X
Urine sample		X				X	X		
Adverse events	X	X	X	X	X	X	X		
Visual outcome and refractive errors								X	X
Retinal morphology with OCT								X	X
Diagnoses and complications								X	X
Study termination		X	X	X	X	X	X	X	X

Study protocol version 4

Visit R0= Visit before start of intervention

Visit C1 = Clinical visit 1 (start of intervention)

Visit R1 = 1 week after start of intervention

Visit R2 = 2 weeks after start of intervention

Visit C2 = Clinical visit 2 (40 weeks PMA)

Visit T1 = 2 weeks after end of intervention

*Abbreviations*: *OCT* Coherence tomography, *PMA* Postmenstrual age, *ROP* Retinopathy of prematurity, *SpO2* Oxygen saturation, *VEGF* Vascular endothelial growth factor

^a^Visit RX = ROP Screening and intervention as many as required in order to be correctly followed-up regarding the monitoring and treatment of the ROP disease, procedures performed weekly

^b^Main study termination visit occurs two weeks after the last intervention or at earliest at 40 weeks PMA when maximum ROP should have occurred

^c^ROP treatment provided when required according to guidelines

^d^Intraocular pressure will be measured before intervention, 1 and 2 weeks after start of intervention and after end of intervention

^e^If performed in clinical routine, PeaPod in Gothenburg

^f^If clinical sample is taken left over blood is collected for analyses

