### Sample size

Natural history studies of ROP suggests that 50% of infants with ROP stage 2 in posterior zone II with haemorrhage or ROP stage 3 in zone II develop Type 1 ROP needing treatment [1]. We aim to reduce the number of infants progressing to severe ROP needing treatment with laser and/or anti-VEGF by 60%. Assuming 50% of infants need ROP treatment in the placebo group and 20% in the dexamethasone group, alpha 0.05, using a two-sided Fisher’s exact test, would require 45 infants to be included per study group (1:1 ratio), in total, 90 infants excluding dropouts, to achieve a power of 80%. Taking into account a 10% drop-out rate, five infants per study group and thus 100 infants in total will need to be included.

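### The protocol states no way to stop study drops for good and keep the infant in follow-up, so Type 1 ROP status may go uncollected for infants withdrawn early

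*Protocol article*

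**What the plan says.** Subject withdrawal lets parents withdraw an infant at any time. It also lets the attending neonatologist or the PI withdraw an infant from the study for safety reasons. The examples are adverse events, major protocol deviations and "significant deteriorations in the patient’s condition that warrant discontinuation of the intervention". So a reason to stop the drops appears as a reason to leave the study. For infants who leave, the instruction is: "The final examination/sampling at study termination must then be performed at the time of the study discontinuation". They are not replaced.

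The safety outcomes section describes what can be done about an adverse event: "The local investigator and PI can stop the intervention temporarily or discontinue the infant from the study". Termination procedures follow in the second case.

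For infants who stay in, a footnote to Table 2 sets the end of the main study: "Main study termination visit occurs two weeks after the last intervention or at earliest at 40 weeks PMA when maximum ROP should have occurred". The section on eligibility, randomization and blinding says: "ROP evaluations will adhere to clinical screening practice according to national guidelines".

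The sample size section plans 45 evaluable infants per group and adds an allowance: "Taking into account a 10% drop-out rate, five infants per study group and thus 100 infants in total will need to be included".

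**The concern.** The primary outcome is whether an infant progresses to Type 1 ROP. The protocol itself places maximum ROP at about 40 weeks PMA. An infant who leaves before then has a last study examination on the day of leaving and may still progress. Screening for ROP is routine care and does not depend on study drops, so the clinical record would normally show what happened. The article provides no means of bringing that information into the trial.

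The listed reasons for withdrawal are not obviously unrelated to the comparison. Adverse events may reflect the drug, and a deteriorating infant may be at higher risk of ROP progression. If withdrawal is linked to either, the infants with a known outcome are a selected group, and the selection may differ by arm. Blinding does not prevent this when the trigger is an effect of the drops. The 10% allowance protects precision down to 45 per arm. It does not protect against bias.

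**Working it through.** **1. The routes stated in the text.**
- Temporary stop of drops: the infant stays in (safety outcomes section).
- Discontinuation from the study: final examination at that time (Subject withdrawal; safety outcomes section).
- Stop of drops when anti-VEGF is planned: no study exit is stated (Intervention; Table 1). Table 1 lists this under Type 1 ROP, so the primary outcome has already occurred and this route does not help here.
- Normal end of drops after tapering or at 12 weeks: termination visit as in the Table 2 footnote.
- Permanent stop for an adverse event, deviation or deterioration, with continued follow-up: not stated.

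**2. Timing.** The planned visit is two weeks after the last drop and not before 40 weeks PMA. A withdrawal examination has no such lower limit. Table 2 also marks ROP evaluation and RetCam at R0, R1, R2 and RX but not at T1, so the termination visit as tabulated does not itself list an ROP assessment.

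**3. The plan's sample size reproduces.** Inputs from the sample size section: 50% vs 20%, two-sided Fisher's exact test, alpha 0.05. Power is the sum, over all pairs of event counts, of the product of the two binomial probabilities where Fisher's p ≤ 0.05.
- 44 per arm: 80.2%. 45 per arm: 81.5%.
- 45 / (1 − 0.10) = 50 per arm, 100 in total.

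The arithmetic is sound.

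**4. Bound on the effect of missing outcomes.** Assumption: all 5 of 50 infants lost per arm are lost through this clause. Observed counts at the planned rates: 0.50 × 45 = 22.5, taken as 23, and 0.20 × 45 = 9.

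| Missing infants who progress (placebo; dexamethasone) | Placebo vs dexamethasone | Fisher p |
|---|---|---|
| not counted | 23/45 vs 9/45 | 0.004 |
| 0 of 5; 5 of 5 | 23/50 vs 14/50 | 0.097 |
| 2 of 5; 5 of 5 | 25/50 vs 14/50 | 0.040 |

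The middle row is the most extreme allocation. If each of the ten infants had an independent 50% risk, its probability would be (1/2)^10 = 1/1024.

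**5. Direction of bias, with assumed inputs.** If a share w of an arm is withdrawn and a fraction q of those progress, the rate among the remainder is (true rate − w × q) / (1 − w). Take a true rate of 50% in both arms and w = 10% in the dexamethasone arm only.
- q = 80%: (0.50 − 0.08) / 0.90 = 46.7%, which falsely favours dexamethasone.
- q = 20%: (0.50 − 0.02) / 0.90 = 53.3%, which falsely favours placebo.

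**6. Power if everyone is followed.**
- 50 per arm, 50% vs 20%: 85.3%. This assumes that stopping early does not raise the 20% rate.
- If 5 of 50 dexamethasone infants stop and revert to 50% risk, the arm rate is (45 × 0.20 + 5 × 0.50) / 50 = 11.5 / 50 = 23%. Power at 50 per arm is then 75.3%.
- For comparison, 45 per arm at 50% vs 20%: 81.5%.

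**The case against.** The strongest reply is that the text permits and does not compel. Infants may be withdrawn; nowhere is every stop of drops called a withdrawal. Temporary stops keep the infant in, and the termination visit after the last drop shows that observation beyond dosing is expected. This stands, and it limits the point to permanent stops for the listed reasons. For those, the only stated alternative to a temporary stop is still exit from the study.

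A reader might infer that the primary analysis will be a comparison of completers, or that the outcomes of withdrawn infants will be discarded. The documents do not say so. No analysis population is defined here, detailed methods are deferred to an SAP that is not shown, and the article condenses a fuller protocol. Silence on analysis sets is therefore not part of the point. What remains is a stated data-collection rule, and an SAP cannot recover outcomes that were never collected.

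A reader might also take the 10% dropout as the expected loss from this clause. The sample size section does not give its causes. Parental withdrawal, death and loss to follow-up could account for some or all of it.

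Nor does the article make raised ocular pressure or abnormal growth a reason to stop. It says they are monitored. Differential withdrawal by arm is plausible, but no figure in the document supports a particular rate.

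**Conclusion.** The point holds in this form: as written, an infant taken off drops permanently for an adverse event, major deviation or deterioration has no stated path to the planned outcome assessment, so Type 1 ROP status may be unsettled and uncollected. The possible bias can go in either direction, and its size cannot be estimated because withdrawal rates and later risks are not given.

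The shift from p=0.004 to p=0.097 is a bound. It rests on charging all ten planned dropouts to this clause and on the most extreme split between arms. With 25/50 vs 14/50 the result stays significant at p=0.040, so a changed conclusion is possible but not shown to be likely.

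It is tempting to add that full follow-up would raise power from 81.5% to 85.3%. That is not supported: the figure needs the 20% rate to hold in infants who stop early, and power falls to 75.3% if 5 of 50 revert to 50% risk. The case for follow-up rests on avoiding bias.

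**What to change.** Amend Subject withdrawal and the safety outcomes section to distinguish *study drops stopped* from *withdrawn from the study*. After drops stop for any reason, continue to record ROP stage, zone, plus disease and any ROP treatment from routine screening up to the planned termination point in Table 2. Include these infants in the primary analysis in the arm to which they were assigned. End data collection only where parents withdraw consent to the use of data. If the full protocol already provides for this, aligning the article's wording is enough.

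The cost is amendment wording, an eCRF field and possibly one line in the consent form. The data come from screening that takes place anyway. The treatment effect may be diluted by infants who stop early, and that should be accepted openly. When drops should be stopped is a clinical matter and is not addressed here.

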### Primary outcome of the intervention study

The primary objective is to evaluate if dexamethasone eye drops, compared to placebo, reduce the proportion of infants with severe ROP from progressing to severe Type 1 ROP needing treatment.

### Secondary outcomes of the intervention study and follow-up

The secondary objectives are to compare the following outcomes between the dexamethasone intervention and placebo:Time from detection of severe ROP to Type 1 ROP.Recurrences after laser/anti-VEGF treatment.Retinal morphology at 40 weeks postmenstrual age (PMA) and at 2 and 5.5 years of age.Change in intraocular pressure from before the intervention to 1–2 weeks after the intervention starts and at the end of the intervention.Visual acuity, refraction, orthoptic and ophthalmological status at 2 and 5.5 years of age.

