### Statistical analysis

All detailed statistical methods will be documented in a statistical analysis plan.

All analyses will be performed using either SAS software version 9.4 or later (SAS Institute Inc, Cary, NC, USA) or SPSS software version 26.0 or later (IBM Corp, Armonk, NY).

For tests between two groups, Fisher’s exact test will be used for dichotomous variables, Mantel–Haenszel Chi-square trend test for ordered categorical variables, Chi-square test for non-ordered categorical variables and Fisher’s nonparametric-permutation test for continuous variables. All efficacy evaluations will be adjusted for centre (strata in randomization) and gestational age (the most prominent risk factor). The difference between the two study arms with respect to binary outcomes such as the primary variable will be evaluated using logistic regression, for time-to-event data using Cox proportional hazards model, for number of recurrences per follow-up time using Poisson regression, for continuous outcomes using analysis of covariance (ANCOVA) or Fisher’s non-parametric permutation in case of not normally distributed data, and continuous outcomes repeatedly measured over time using mixed models for repeated measures.

All tests will be two-tailed. The primary analysis will be considered confirmed if *p* < 0.05.

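### Baseline intraocular pressure is measured but is not among the stated covariates for the change-in-pressure outcome; adding it would gain precision at no cost

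*Protocol article*

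**What the plan says.** The section on secondary outcomes lists, for comparison between dexamethasone and placebo, "Change in intraocular pressure from before the intervention to 1–2 weeks after the intervention starts", and also at the end of the intervention.

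Footnote d of Table 2 sets the schedule: "Intraocular pressure will be measured before intervention, 1 and 2 weeks after start of intervention and after end of intervention". A pre-treatment value is therefore planned for each infant.

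The Statistical analysis section makes five relevant statements:

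- Two-group tests use "Fisher’s nonparametric-permutation test for continuous variables".
- On adjustment: "All efficacy evaluations will be adjusted for centre (strata in randomization) and gestational age (the most prominent risk factor").
- Differences between arms are evaluated "for continuous outcomes using analysis of covariance (ANCOVA) or Fisher’s non-parametric permutation in case of not normally distributed data".
- The same sentence assigns "continuous outcomes repeatedly measured over time using mixed models for repeated measures".
- The section opens by deferring detail: "All detailed statistical methods will be documented in a statistical analysis plan". That plan is not shown.

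None of these names the baseline value of a continuous outcome as a covariate.

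**The concern.** The outcome is defined as a change and the baseline is collected, yet the two covariates the plan names do not include it. A difference between two readings carries the measurement noise of both. Subtracting the baseline also over-corrects for chance imbalance at the start whenever the correlation between readings is below 1. Regressing on the baseline avoids both problems.

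Precision matters more than usual for this outcome. The article's Discussion names raised intraocular pressure as a common ocular side effect of short-term topical dexamethasone, first noticed in the first two weeks. The safety section singles out pressure above 20 mmHg for monitoring. For a possible harm, an imprecise comparison makes it more likely that a real rise is reported as no clear difference. The trial was sized for the binary primary outcome, with no calculation for pressure, so there is no planned margin to absorb the loss.

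**Working it through.** **The plan's own figure.** The Sample size section assumes 50% versus 20%, two-sided alpha 0.05, Fisher's exact test and 80% power, and states 45 evaluable infants per group. The continuity-corrected formula for two proportions gives 45 per group. Exact enumeration of the Fisher test gives 81.5% power at 45. Allowing 10% dropout, 45/0.9 = 50 per group, 100 in total. The stated size reproduces. It concerns the primary outcome only and is used below just for the 45 per arm.

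**Inputs for pressure.** The article gives no standard deviation, target difference or correlation. I work in units of the standard deviation, taken as equal at baseline and follow-up, and assume a range for the correlation rho.

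**Formulas** (per infant, in SD² units):

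- Variance of an unadjusted change score: 2(1 − rho).
- Residual variance after ANCOVA on baseline: 1 − rho² = (1 − rho)(1 + rho).
- Ratio of ANCOVA to change: (1 + rho)/2, which is below 1 for every rho below 1.

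Fix the true difference so that a two-sided 5% test of change has 80% power. The standardised effect is then 1.960 + 0.842 = 2.802. Under ANCOVA it becomes 2.802/√[(1 + rho)/2], and power is Φ of that value minus 1.960.

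Example at rho 0.5: the ratio is 0.75, 2.802/0.866 = 3.235, 3.235 − 1.960 = 1.275, and Φ(1.275) = 89.9%.

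| Assumed rho | Variance ratio | ANCOVA power when change has 80% | Change-score power when ANCOVA has 80% | Infants per arm for change to match ANCOVA at 45 (45/ratio) |
|---|---|---|---|---|
| 0.3 | 0.65 | 93.5% | 62% | 69 |
| 0.5 | 0.75 | 89.9% | 68% | 60 |
| 0.7 | 0.85 | 86.0% | 73% | 53 |
| 0.8 | 0.90 | 84% | 76% | 50 |
| 0.9 | 0.95 | 82% | 78% | 47 |

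The fourth column runs the calculation in reverse, as Φ(2.802 × √ratio − 1.960). The gain over 80% is 13.5 points at rho 0.3, about 10 at 0.5, 6 at 0.7, 4 at 0.8 and 2 at 0.9.

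**Which stated route includes the baseline?**

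- Permutation test: no covariates are described, so on the outcome as defined it compares unadjusted change.
- ANCOVA: the stated covariates are centre and gestational age. Baseline pressure could be added but is not named.
- Mixed model for repeated measures: baseline can enter as a covariate or as one of the responses. The text specifies neither.

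**The case against.** The strongest reply is that this is detail the article openly leaves to the SAP. The adjustment sentence gives factors common to all efficacy outcomes, including binary and time-to-event ones that have no baseline value, so an outcome-specific baseline would not be expected in it. Pressure is measured repeatedly, and the plan already assigns repeated continuous outcomes to mixed models, which can handle a baseline. Defining the outcome as change does not fix an unadjusted analysis either: ANCOVA on change with baseline as covariate gives the same treatment effect as ANCOVA on the follow-up value.

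Much of this stands. A reader might infer that the plan excludes baseline pressure and commits to a raw change score. The documents do not support that. The covariate sentence is not worded as exclusive, and two of the named methods can include the baseline. A reader might also infer that pressure, being a safety measure, falls outside the adjusted models and gets the permutation test by default. That is not settled either. Change in pressure is listed as a secondary outcome beside time to Type 1 ROP, the safety section carries the separate threshold of 20 mmHg, and the sentence on differences between arms does not exclude pressure.

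What the reply does not remove is narrower. The plan states a covariate set and a permutation route, and neither includes a value that is already collected and would sharpen the comparison.

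**Conclusion.** The point holds as a free improvement of low severity. Baseline pressure is not among the stated covariates, and the permutation route describes no baseline adjustment. If change were compared without the baseline, the variance would be larger by a factor of 2/(1 + rho). In the calculation above, 80% power by change score corresponds to about 94% down to 82% by ANCOVA as rho runs from 0.3 to 0.9.

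The size rests on an assumed rho, equal standard deviations at the two times, and a normal approximation. If pressure readings are highly correlated within an infant, the gain is only 2 to 4 points. It is also conditional on the baseline actually being omitted, which the article does not say.

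It would be wrong to conclude that the comparison is biased: randomisation keeps a change-score comparison unbiased, and only precision is at issue. The primary analysis, the alpha level and the sample size of 100 are untouched.

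**What to change.** In the Statistical analysis section or the SAP, state that intraocular pressure at weeks 1 and 2 and at the end of intervention is compared between arms with the mixed model (or ANCOVA) already named, with baseline pressure added to centre and gestational age. Report the adjusted mean difference with its 95% confidence interval. If the permutation test is kept for non-normal data, say how the baseline enters there too, for example by permuting residuals after adjustment.

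The cost is one or two sentences. The baseline reading is already scheduled, so no visit, measurement or infant is added, and the validity of the comparison is not affected.
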